#### Blinding

It is not possible to blind the participants to group allocation for psychological interventions, while the RA who is responsible for the post-test data collection will be blinded. Participants' personal identifiers will be excluded from the dataset.

#### Assessment

Timeline of overall evaluation plan on intervention effectiveness is shown in Figure 2. All participants will complete a 30-minute face-to-face survey comprising a set of assessment on psychological stress, well-being, and other relevant outcomes before the intervention and after the 8-week intervention. To minimize the survey effect and to assess the long-term effects, we will also conduct a phone interview as a follow-up survey at two months after the intervention.

The VR-based MBI group will also participate in two face-to-face, 60-minute, audio-recorded focus group discussions—one immediately after the intervention and another at the two-month follow-up—to provide in-depth feedback on their experience with the intervention. These discussions will help us understand the impact of the VR-based MBI and identify any potential benefits or challenges.

All face-to-face surveys and focus groups will be organised and taken place at Lingnan University.

**Figure 2 Evaluation timeline**

|                                | T0 Before intervention
(pretest)                                                                                                                                                                                                                                                                        | T1 After 8-week intervention
(post-test)                                                                                                                                                                                                                                                                                                  | T2: 2-month after intervention
(Follow-up)                                                                                                                                                                                                                 |
|--------------------------------|--------------------------------------------------------------------------------------------------------------------------------------------------------------------------------------------------------------------------------------------------------------------------------------------------------------------|------------------------------------------------------------------------------------------------------------------------------------------------------------------------------------------------------------------------------------------------------------------------------------------------------------------------------------------------------|-----------------------------------------------------------------------------------------------------------------------------------------------------------------------------------------------------------------------------------------------------------------------|
| Quantitative assessment | T0 face-to-face survey
Site: Lingnan University                                                                                                                                                                                                                                                                 | T1 face-to-face survey
Site: Lingnan University                                                                                                                                                                                                                                                                                                   | T2 Phone survey                                                                                                                                                                                                                                                       |
| Assessment tool                | 
 
• Basic information (pre-test only)
 
• DASS21
 
• EQ-5D-5L
 
• CZBI
 
• EQ-5D-5L-proxy (Quality of life of care recipients)
 
• Five Facet Mindfulness Questionnaire
 
• ONS4
 
• Relationship Closeness Scale
 
 | 
 
• DASS21
 
• EQ-5D-5L
 
• CZBI
 
• EQ-5D-5L-proxy (Quality of life of care recipients)
 
• Five Facet Mindfulness Questionnaire
 
• ONS4
 
• Relationship Closeness Scale
 
• Treatment Acceptance/Adherence (post-test for VR group only)
 
 | 
 
• DASS21
 
• EQ-5D-5L
 
• CZBI
 
• EQ-5D-5L-proxy (Quality of life of care recipients)
 
• Five Facet Mindfulness Questionnaire
 
• ONS4
 
• Relationship Closeness Scale
 
 |
| Qualitative assessment  |                                                                                                                                                                                                                                                                                                                    | Focus group (VR group only)
Site: Lingnan University                                                                                                                                                                                                                                                                                              | Focus group (VR group only)
Site: Lingnan University                                                                                                                                                                                                               |

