**b. Aim and Objectives:**

This pilot study aims to explore the feasibility, acceptability and efficacy among dementia caregivers of the MBI delivered by VR technology (VR-based MBI) in the home environment. The specific research questions and hypotheses are as follows:

- **How do dementia caregivers perceive VR-based MBI?**

We will explore the feasibility, acceptability and understanding of using VR technology or audio to learn MBI among caregivers of people with dementia through a focus group qualitative study and a quantitative study using the Treatment Acceptability/adherence Scale. The readiness of caregivers to practice MBI at home after observing group sessions will also be explored.

- **Does the VR-based MBI offer additional benefits to psychological well-being compared with audio-based MBI and usual care?**

We will address this question through a 3-arm pilot randomized controlled trials (RCT). Using an 8-week audio-based MBI protocol and usual care as comparing conditions. We hypothesize that among caregivers of people with dementia:

**HP1:** The VR-based MBI group will show greater improvement in psychological well-being (**Primary Outcome**) than the audio-based MBI group, while the audio-based MBI group will show greater improvement than waitlist control group

Psychological well-being will be assessed through depression, anxiety and stress, as well as general wellbeing.

- **Does the VR-based MBI offer additional benefits to caregivers' mindfulness and quality of life, care recipients' quality of life and the relationship between caregiver and care recipient, compared with audio-based MBI and usual care?**

We will address this question through the RCT mentioned above. Compared with the audio-based MBI and usual care groups, we hypothesize that:

**HP2:** The VR-based MBI group will show greater improvements in caregiver burden, mindfulness level, and quality of life (**Secondary Outcomes**) than the audio-based MBI group, while the audio-based MBI group will show greater improvement than waitlist control group;

**HP3:** The relationship between VR-based MBI group caregivers and the care recipients (**Secondary Outcomes**) will show greater improvement than the audio-based MBI group, while the audio-based MBI group will show greater improvement than waitlist control group;

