### Intervention and control groups

#### **A) VR-based MBI group (Intervention group)**

Upon enrolment in the study, participants assigned to the VR-based MBI group will be invited to a briefing session at Lingnan University. The session will take place in a quiet room with suitable lighting and air conditioning. Following the participants' written informed consent, they will be introduced to the VR-based MBI user manual, VR technology after completing a pre-test survey.

During the briefing session, participants will download the VR-based MBI app developed by our research team and familiarize themselves with wearing the JAPAN JTSK 6th generation upgraded version of 3D virtual reality glasses. They will engage in a 5-10 minute exercise within the VR environment, giving them the opportunity to explore different natural sceneries provided

in the app. This exercise aims to acclimate participants to the VR technology and allow them to select environments for their mindfulness practice at home. Participants will be provided with the VR glasses to take home and practice mindfulness for approximately 10-15 minutes daily over the next eight weeks. The app will record their practice time for further analysis. Weekly telephone follow-ups will be conducted to address any questions or concerns, and reminder messages will be sent once a week.

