**(v) Indicators and targets**

- **Reach**

Reach indicators encompass the number of dementia caregivers who express interest in participating and those who actually engage in the program, and the representativeness of participants considering their demographic characteristics.

Qualitative feedback on barriers and facilitators affecting recruitment will be gathered from participants and local stakeholders.

- **Effectiveness**

Overall evaluation plan is shown in Figure 2.

Evaluation of the feasibility and acceptance of VR-based MBI

(Quantitative indicator) At the completion of the intervention, the intervention group will be interviewed to evaluate the acceptability and feasibility of VR-based MBI using the Treatment Acceptability/ Adherence Scale with 10 items (31) .

(Qualitative indicator) Participants will be invited to discuss their experiences of MBI via the VR technique, enabling their comments and suggestions to be collected, and the pros and cons of the VR technique discussed.

Evaluation of efficacy of VR-based MBI

(Quantitative indicators) The primary outcomes will be participants' psychological well-being (measured by the Depression, Anxiety, Stress scale (21 items) (32) and the Chinese Version of the Personal Well-being ONS4 (4items) (33). The secondary outcomes will include (a) Cantonese Zarit Burden Scale Short Version (34); (b) caregivers' health-related quality of life measured by the EUROHIS-QOL 5-Item Index (35); (c) caregivers' mindfulness level measured by the five-facet mindfulness questionnaire (36) ; and (d) carer-patient relationship measured by the Relationship Closeness Scale (37).

- **Adoption**

At the setting level, quantitative adoption indicators will encompass the percentage of participants from various recruitment channels, reasons for setting exclusions, participation rates of approached settings, and a comparison of participating settings with non-participants based on characteristics.

At the staff levels, adoption evaluation will involve gathering qualitative feedback on intervention delivery, such as reasons driving adoption or non-adoption of the intervention, and how the intervention could be integrated into their existing practices and services, along with their feedback on the potential for broader adoption within their organisation or beyond.

For caregivers, qualitative methods will be employed to assess their participation and experiences during the intervention period.

- **Implementation**

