Implementation will be evaluated by monitoring the percentage of intervention sessions that are delivered as intended, any adaptations made to the intervention during the study, any additional costs incurred, and the consistency of intervention delivery across different study arms.

We will also collect qualitative feedback on the barriers and facilitators encountered during the implementation process and the overall challenges faced by participants and staff.

- **Maintenance**

Maintenance will be assessed by tracking the retention rate of participants who continue to engage with the VR-based mindfulness intervention beyond the initial trial period. We will conduct a 2-month follow-up assessment to evaluate whether the benefits observed during the study are sustained over time. Additionally, we will gather qualitative feedback from multiple stakeholders to assess the intervention's integration into existing practice and the support required to maintain intervention effectiveness.

(vi) **Evaluation plan (RE-AIM framework)**

- **Reach of the target population**

During the recruitment and implementation, we will track the number of dementia caregivers who show interest in the program and those who proceed to participate. We will also collect demographic data from participants to assess how well they represent the target population of dementia caregivers in Hong Kong. Additionally, we will gather qualitative data through weekly call, focus groups and stakeholder interviews to understand the factors that influence recruitment and participation.

- **Effectiveness (or Efficacy)**

Evaluation of the feasibility and acceptance of VR-based MBI

After completing the 8-week intervention, the VR-based MBI group will participate a survey to evaluate the acceptability and feasibility. Meanwhile, a longitudinal **qualitative** element of the study will be included by undertaking face-to-face focus group discussions with participants in the VR-based MBI group at the completion of the intervention and at 2-months follow-up. It is envisaged there will be 3-4 focus groups, each including 5-6 participants, at each timepoint. The PA and Co-As will facilitate the focus group discussions employing a semi-structured interview method will be adopted. The group discussions will be audio-recorded.

Evaluation of efficacy of VR-based MBI

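### The acceptability objective covers VR and audio, but the acceptability scale and the focus groups are planned in the VR arm only

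*Protocol*

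**What the plan says.** Section b (Aim and Objectives), under the first research question: "We will explore the feasibility, acceptability and understanding of using VR technology or audio to learn MBI among caregivers of people with dementia". The tools named there are a focus group study and "a quantitative study using the Treatment Acceptability/adherence Scale".

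The operational sections are narrower:

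- Figure 2, T1 column: "Treatment Acceptance/Adherence (post-test for VR group only". The focus group row is also marked as VR only, at T1 and T2.
- Section c(v), Effectiveness: "the intervention group will be interviewed to evaluate the acceptability and feasibility of VR-based MBI", using the 10-item scale.
- Section c(vi), Effectiveness: the acceptability survey and the focus groups are again for the VR group. The Assessment section says the same of the focus groups.

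On practice time, the VR arm section states: "The app will record their practice time for further analysis". The audio arm section mentions neither an app nor a log. It does say that the audio arm receives similar reminders and telephone follow-ups, and that the two active arms differ only in the VR technology. Section c(v) lists "the consistency of intervention delivery across different study arms" as an implementation indicator, and section c(vi) names app time records and weekly calls among the sources.

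On blinding: "the RA who is responsible for the post-test data collection will be blinded".

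**The concern.** The objective names two media, and both tools named for it are given in only one of them. The schedule is fixed in the protocol, so no later analysis plan can recover scores that were never collected.

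Feasibility and acceptability come first in this pilot's stated aim, and the audio arm exists to isolate what VR adds to the same mindfulness instruction. A TAAS mean from the VR arm alone cannot show whether caregivers accept the headset or the mindfulness content that both arms share.

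Two smaller matters go with this. A scale given to one arm inside the T1 survey may tell the assessor which arm the participant is in. And unless practice time is recorded in the same way in both active arms, practice cannot be described like for like.

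**Working it through.** **Coverage of the objective**

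| Tool named for the objective | VR arm | Audio arm | Where fixed |
|---|---|---|---|
| TAAS, 10 items, T1 | yes | no | Figure 2; c(v); c(vi) |
| Focus groups, T1 and T2 | yes | no | Assessment; Figure 2; c(vi) |

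The only remaining source on audio acceptability is informal feedback in the telephone follow-ups, which gives no score.

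**Inputs.** 30 participants per arm, from section c(i); 3 × 30 = 90 agrees with the stated total. The protocol gives no SD for the TAAS, so results are in SD units. It gives no dropout rate either; I assume 20% for illustration, so 30 × 0.8 = 24 per arm. Alpha of 0.05 two-sided and power of 80% are also my assumptions. The protocol states no precision or power figure for acceptability, so there is none to reproduce.

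**As planned (30 VR, 0 audio).** Only a one-arm mean is available. The 95% half-width is t(0.975, 29)/√30 = 2.045/5.477 = 0.37 SD. The VR-minus-audio difference is not estimable.

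**With the scale in both active arms.** The half-width for a difference of two means is t(0.975, 2n − 2) × √(2/n).

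- n = 30: 2.002 × 0.2582 = 0.52 SD
- n = 24: 2.013 × 0.2887 = 0.58 SD

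The difference detectable with 80% power is about (1.960 + 0.842) × √(2/n).

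- n = 30: 2.802 × 0.2582 = 0.72 SD
- n = 24: 2.802 × 0.2887 = 0.81 SD

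The comparison would therefore be descriptive. That suits a pilot meant to inform a larger trial, but it would not support a test.

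**Practice time.** The VR section describes app logging and the audio section describes none. However, every participant must own a phone that can run the app, the audio track is the one in the app, and section c(vi) does not limit app records to one arm. The text leaves audio logging open; it does not rule it out.

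**Blinding.** The VR-only scale sits in the T1 assessment list, and post-test collection is by a blinded RA. It is listed last, but the protocol fixes neither an order of administration nor who gives it.

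**The case against.** The strongest reply is that the scope is deliberate. The heading of the research question asks how caregivers perceive VR-based MBI, the overall aim concerns MBI delivered by VR, and none of HP1 to HP3 concerns acceptability. Figure 2, c(v) and c(vi) all agree on VR only, which makes the mention of audio in section b the outlier. This stands in part: the gap lies in an exploratory objective, and narrowing the wording would remove the contradiction. It does not remove the need to choose, because the objective as written commits the trial to both media.

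A reader might go further and infer that audio practice is not recorded at all, and so that delivery cannot be compared between arms. The documents do not support that. They are silent on audio logging, the indicator concerns delivery rather than minutes practised, and the audio arm also receives telephone follow-ups.

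A reader might also infer that assessor blinding fails. That is not shown. If the scale comes last, the T1 outcomes are already recorded, and the protocol does not say that the blinded RA gives it. The DASS-21 and ONS4 are in any case reported by participants who know their arm, which limits the extra bias. The risk is conditional, but the plan does nothing to exclude it.

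Lastly, a VR-audio difference in outcome could not be divided into an effect of VR and an effect of more practice merely by logging minutes, because practice occurs after randomisation. The randomised contrast still estimates the total effect. Common logging serves description only.

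**Conclusion.** The contradiction on acceptability holds. Section b covers VR and audio, while the scale and the focus groups are confined to VR, so audio acceptability has no planned score and the VR-minus-audio difference cannot be estimated. With the scale in both active arms, the 95% half-width would be about 0.52 SD at 30 v 30, or about 0.58 SD under an assumed 20% loss.

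The other two parts hold only in a weaker form: audio practice-time capture is unspecified rather than absent, and disclosure of allocation through the scale is a risk that depends on who gives it and when. HP1 to HP3 are not affected by the missing acceptability data. The change is worth making before recruitment because it is cheap and the data cannot be recovered afterwards.

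**What to change.** 1. Give the TAAS at T1 to both the VR and audio arms, worded so that it fits either medium, and amend Figure 2, c(v) and c(vi) to match. Report the difference with its 95% confidence interval as descriptive. If the focus groups stay VR only, say in section b that the qualitative part covers VR alone.
2. Failing that, limit the section b objective to VR.
3. Have the scale completed after all outcome scales, on a sealed form or with unblinded staff. This is still needed once both active arms receive it, because its absence would mark out the waitlist arm.
4. State how practice minutes are recorded in the audio arm, and use one method in both active arms: either the same app or a question in the telephone follow-ups that both already receive.

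The cost is ten extra items for the 30 audio participants, a slightly longer T1 visit for them, and one question per call if the telephone route is used.

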#### Incentives for participants

For your participation, you will receive a HK\$100 supermarket coupon after completing pre and post-test and an additional HK\$50 coupon after completing a follow-up phone survey at two months after intervention. If you are in the VR-based MBI group and participate in the focus group discussions, you will be given an additional HK\$50 supermarket coupon for each session you attend.

### **(iii) Contingency/alternative plan if any problem encountered during implementation**

#### Possible adverse effects of using VR

The common adverse effects of using VR include nausea, eye fatigue (41), dizziness, headache, and motion sickness.(30) The fixed background and short practice time will reduce these adverse effects. During the design stage of the VR-based MBI, relevant procedures will be followed to reduce the adverse effects of using VR and to increase participants' static balance. To manage potential motion sickness, we will prioritize user comfort by gradually exposing participants to VR environments. Additionally, we will optimize the VR experience with stable, natural environments, maintain high frame rates, and provide guidance on minimizing discomfort, including hydration and potential use of ginger supplements or anti-nausea medications.

All participants will be asked at the practice reminders and follow-up if they suffer these side effects. If so, the counsellor will provide counselling on usage of the equipment. If the side effects are severe, the counsellor will ask them to cease use. If a participant reports experiencing emotional difficulty, the research team will also refer them to a specialist or other counsellor.

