### a. Justification for Conducting the Project:

#### (i) Health needs of the local community

As the global population ages, the growing prevalence of dementia has become a worldwide public health concern (1). Dementia, a progressive disorder, leads to deteriorating perceptual and cognitive abilities, behavioral changes, and loss of independence (2). Dementia impairs patients' social or occupational functioning and is a major cause of disability in older age. These symptoms not only impact the quality of life of people with dementia but also cause psychological distress for their caregivers (2,3). Currently, 50 million people live with dementia worldwide, which is predicted to rise to 82 million by 2030(4). An ongoing modelling study (5), which is part of a larger project named, "Tools to Inform Policy: Chinese Communities' Action in Response to Dementia (TIP-CARD)" shows that 178,139 people aged 60 years and older live with dementia in Hong Kong in 2021, and over 70% of dementia costs relate to informal care.

Dementia care largely rely on informal caregivers, such as family members, friends, and neighbors. These caregivers are vital partners in the health system and contribute to the realisation of healthy ageing and aging-in-place initiatives. In Hong Kong, over 62.6% of people with dementia have at least two informal caregivers (5). With input from multiple informal carers, the average informal care time amounts to 400 hours per month, 40% of which is attributed to managing behavioral and psychological symptoms of dementia and ensuring their safety (supervision time) (5).

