Dementia caregivers bear significant daily caregiving responsibilities and dedicate the majority of their time to companionship and ensuring the safety of people with dementia. This responsibility often leaves caregivers with limited time and availability to engage in mindfulness practice outside of the home. However, the practice of mindfulness requires conscious effort and can be difficult to maintain in the home environment, especially for novice meditators who are already expending cognitive resources to control their self-regulatory skills (13). Beginning mindfulness practitioners commonly report easily being distracted during practice, fall asleep, wrestle with tiredness or ambivalence, difficulty of incorporating mindfulness practice into their daily life (14). The adoption of digital technology may support beginners' mindfulness practice, such as Web-based interventions (15) or smartphone apps (16) that can deliver guided audio-recorded mindfulness practice in facing the challenges of practicing and adhering to mindfulness (17). However, there are limitations with these audio-based MBIs, including a low adherence rate and the failure of participants to maintain these practices over the long term (17).

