**(iii) How will this project add value to existing evidence in addressing the health needs of the local community?**

Virtual reality (VR) is an immersive technology that may boost the advantages of mindfulness meditation and facilitate participants' attention management. It refers to the use of a headset to create a 360-degree virtual environment, incorporating realistic 3D graphics, stereoscopic viewing, and head tracking (18). The use of VR technology with natural environments embedded in the system to assist mindfulness practice is supported by attention restoration theory (ART) (19). Natural stimuli in VR have the potential to reduce mental fatigue and increase attention (20). Additionally, nature can enhance ecological behavior, both in real-world and virtual experiences (21). The immersive nature of VR blocks distractions, allowing participants to focus solely on mindfulness practice (18).

VR-based mindfulness practice in a pleasant and immersive virtual environment may relieve physical and mental discomforts frequently experienced by beginning mindfulness practitioners without compromising their present-moment awareness (20). It also provides access to physically or cognitively inaccessible stimuli, enhancing guided imaginary mindfulness (21). Furthermore, VR also facilitates participants' application of mindfulness skills to real-life practice, and its non-traditional format may further increase their acceptance of the therapy (20).

VR-based MBI has recently been proposed as a medium to support mindfulness practice and become an effective way to improve participants' psychological well-being and cultivate spiritual experiences, especially strong feelings of awe (22). Specifically, compared to audio-based mindfulness, VR-based MBIs have been shown to offer several additional benefits, including improved well-being (23), higher treatment adherence (24), reductions in vigor, fatigue, and confusion (25) and more enjoyable experiences (26). However, VR-based mindfulness practice studies are predominantly conducted in a clinic environment or specific settings rather than a home environment (20). Practicing in home environment may enable participants to feel safe and remove their concerns about leaving the person with dementia. VR-based MBI practice can be time- and cost-efficient, simple to initiate and complete, and practical for caregivers at home.

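### Solicited harms are limited to five headset symptoms in the caregiver; falls during practice and incidents involving the care recipient are not specifically asked about or recorded

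*Protocol*

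**What the plan says.** Harm collection is described in one place, Protocol section c(iii), under Possible adverse effects of using VR. The list begins "The common adverse effects of using VR include nausea, eye fatigue" and continues with dizziness, headache and motion sickness. The enquiry that follows is tied to that list: "All participants will be asked at the practice reminders and follow-up if they suffer these side effects". The stated responses are counselling on use of the equipment and, for severe effects, a request to cease use. The same section adds a second route: "If a participant reports experiencing emotional difficulty, the research team will also refer them to a specialist or other counsellor". Static balance appears there as an aim at the design stage, without a question about falls.

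Other sections describe the setting:

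- **Target group:** participants are primary informal caregivers giving more than four hours of care a day to someone living in the community with mild-to-moderate dementia.
- **Section a(ii):** caregivers are said to "dedicate the majority of their time to companionship and ensuring the safety of people with dementia".
- **Section a(iii):** the headset is favoured because "The immersive nature of VR blocks distractions, allowing participants to focus solely on mindfulness practice". Home practice is presented as easing the worry of leaving the person with dementia.
- **VR-based MBI group:** participants are to "practice mindfulness for approximately 10-15 minutes daily over the next eight weeks".

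**The concern.** Taken together, these sections put a person with a supervising role into an immersive headset, at home, every day for eight weeks. The solicited harm question covers how that person feels in the headset. It does not cover whether the caregiver fell or struck something, or whether anything happened to the person with dementia during a session.

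This matters because feasibility is the first aim of the pilot and home use is the novelty claimed in section a(iii). An incident during practice bears directly on feasibility at home. If it is not collected in a defined way, no later analysis plan can recover it, and the larger trial that the pilot is meant to inform would start without it.

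**Working it through.** The protocol states no harm rate or safety target, so there is no figure to reproduce. The check has two parts: a comparison of the sections, and a calculation of scale.

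**1. What each source of information would capture**

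| Source | What it covers | Fall or care-recipient incident during practice? |
|---|---|---|
| Side-effect question, c(iii) | Five symptoms in the headset user | Not asked |
| Emotional difficulty, c(iii) | Acted on if the participant reports it | Not asked |
| Weekly calls, VR and audio arms | Open queries | Could surface; no fixed item or record |
| Focus groups, VR arm | Experience, benefits and difficulties | Could surface; no comparator arm |
| Implementation feedback, c(v) and c(vi) | Barriers and difficulties, qualitative | Could surface; no count by arm |
| EQ-5D-5L proxy at T0, T1, T2 (Figure 2) | Care recipient's quality of life | Does not record an event or link it to a session |

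The focus groups are planned as 3–4 groups of 5–6 people, so 3 × 5 = 15 to 4 × 6 = 24 of the 30 VR participants. None of the RE-AIM indicators in c(v) is a count of safety events.

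**2. Planned exposure in the VR arm**

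Inputs: 30 participants per arm (Target group); 10–15 minutes daily for eight weeks (VR-based MBI group). Full adherence is assumed.

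- Sessions per participant: 8 × 7 = 56.
- Sessions in the arm: 30 × 56 = 1,680.
- Hours per participant: 56 × 10/60 = 9.3 to 56 × 15/60 = 14.
- Hours in the arm: 1,680 × 10/60 = 280 to 1,680 × 15/60 = 420.

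The waitlist arm is offered VR after its control period. That adds exposure, but the dose and uptake are not stated, so it is not counted here.

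**3. What counts from 30 participants could show**

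If all 30 were asked and none reported an incident, the one-sided exact 95% upper bound on the per-participant risk would be 1 − 0.05^(1/30) = 0.095, about 9.5%.

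The documents give no incident rate, so the true risk p has to be assumed. The chance that at least one of 30 is affected is 1 − (1 − p)^30:

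| Assumed p | Chance of at least one affected |
|---|---|
| 1% | 26% |
| 2% | 45% |
| 5% | 79% |
| 10% | 96% |

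These figures show scale. The point does not depend on them.

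**The case against.** The strongest reply is that the protocol is less closed than the symptom list suggests. Weekly calls invite open queries in the VR arm, and the audio arm also receives telephone follow-up. Focus groups and implementation feedback ask about difficulties. A serious incident might well be mentioned. This stands: a reader might infer that such an event could not come to light, and the documents do not support that. What remains is that no item asks for it and no defined record or count by arm results.

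Three further strong readings also fail.

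- **That the audio arm is outside harm enquiry.** The side-effect question is addressed to all participants, and the audio arm receives reminders and calls. Nor does the protocol say how audio users practise, so it cannot be assumed that they keep watch during a session.
- **That the overlap of sessions with supervision can be calculated.** Section a(i) gives 400 hours of informal care a month, "40% of which is attributed to managing behavioral and psychological symptoms of dementia and ensuring their safety (supervision time"), which is 400 × 0.40 = 160 hours. A reader might assign all of it to the participant. But the 400 hours is a total across several carers, and the same section says that over 62.6% of people with dementia have at least two. No time of day is fixed for practice, so the overlap is unknown.
- **That the headset demonstrably isolates the caregiver from the care recipient.** This is a reasonable inference from the rationale in section a(iii), not a statement about how sessions will be run. Sessions are short, and caregivers of people with severe dementia are excluded.

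It is also fair to say that counts from 30 per arm could hardly support a comparison between arms. That limits what the counts can be used for, but it is not a reason to leave the events unrecorded.

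**Conclusion.** The point holds as a gap in what is systematically collected. Followed as written, the plan asks about five headset symptoms and responds to emotional difficulty when it is volunteered. Falls, collisions and care-recipient incidents during practice would reach the record by chance. The gap applies to 1,680 planned home sessions, assuming 30 VR participants and full adherence. How many of these coincide with supervision cannot be derived from the documents, and no incident rate is given.

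This is a matter for the protocol, because it concerns data collection rather than analysis. It does not invalidate the trial or its efficacy comparisons. It does leave a finding of feasibility at home without information that the protocol's own rationale makes relevant. The change should be made.

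**What to change.** Extend the existing side-effect question on the weekly calls, in both the VR and audio arms, with one fixed item: since the last call, was there any fall, collision or injury to the participant, or any incident involving the care recipient, during or just after a session? Keep a dated record of each report, send it to the investigator, and present descriptive counts by arm beside the feasibility results.

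The item should be put by the caller, who is unblinded, and not added to the T1 survey. The Blinding section keeps the post-test data collector unaware of allocation, and a question about sessions could reveal it.

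The cost is slightly longer calls, one extra record form and one more row in the results, with no added visits. The counts would be descriptive: zero events in 30 would still be compatible with a per-participant risk of up to about 9.5%. No rule on care arrangements or on stopping use is proposed here.
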